## Abstract

**Background:**

Early Childhood Caries (ECC) is a widespread problem in Australian Aboriginal communities causing severe pain and sepsis. In addition dental services are difficult to access for many Aboriginal children and trying to obtain care can be stressful for the parents. The control of dental caries has been identified as a key indictor in the reduction of Indigenous disadvantage. Thus, there is a need for new approaches to prevent ECC, which reflect the cultural norms of Aboriginal communities.

**Methods/Design:**

This is a Phase II single arm trial designed to gather information on the effectiveness of a dental health education program for Aboriginal children aged 6 months, followed over 2 years. The program will deliver advice from Aboriginal Health Workers on tooth brushing, diet and the use of fluoride toothpaste to Aboriginal families. Six waves of data collection will be conducted to enable estimates of change in parental knowledge and their views on the acceptability of the program. The Aboriginal Health Workers will also be interviewed to record their views on the acceptability and program feasibility. Clinical data on the child participants will be recorded when they are 30 months old and compared with a reference population of similar children when the study began. Latent variable modeling will be used to interpret the intervention effects on disease outcome.

**Discussion:**

The research project will identify barriers to the implementation of a family centered Aboriginal oral health strategy, as well as the development of evidence to assist in the planning of a Phase III cluster randomized study.

**Trial registration:**

ACTRN12612000712808

## Background

Dental decay (caries) is a widespread disease within Aboriginal communities and it has a particularly severe impact on Aboriginal children. Recent health examinations conducted by medical and nursing personnel in the Northern Territory found early childhood caries to be the most common condition of Aboriginal children, affecting 43% of those examined
[1]. In the context of the limited availability of dental personnel within many Aboriginal communities and due to the thin layer of enamel on primary teeth, dental caries can progress to the rapid destruction of the dentition. This is reflected in the high rates of hospitalisation of Aboriginal children requiring multiple dental extractions under paediatric general anaesthesia
[2-4].

In recognition of the extent and severity of early childhood caries, its high hospitalisation rates and its impact on childhood nutrition, socialisation and schooling, the control of dental caries has been identified as a key indicator in the reduction of Indigenous disadvantage
[5]. Yet the oral health of Aboriginal children is worsening rather than improving under current approaches, with increasing numbers of decayed, missing and filled teeth being found in this population. Indigenous children have twice the levels of dental caries in both their primary and permanent teeth compared with their non-Indigenous counterparts, as well as higher levels of untreated decay
[6].

Many Aboriginal communities face this burden of oral disease with limited or no access to dental services, and current workforce projections predict a worsening shortage of dental personnel
[7]. In addition few Aboriginal Controlled Community Health Services (ACCHS) are funded to provide dental care, and those that do have difficulty in attracting and retaining dental professionals, particularly in rural and remote Australia. Therefore there is an urgent need for the development of effective new approaches to prevent early childhood caries, which are appropriate to the needs of Aboriginal families and can be delivered within the limited resources of the ACCHSs.

After extensive consultation with a number of Aboriginal Controlled Community Health Service staff and the Director of the National Aboriginal Health College a promising family focused dental health education program has been developed. It will be delivered by Aboriginal Health Workers (AHSs) inviting Mothers with young children to an appropriate local ACCHS clinic to offer diet advice, ensure fluoride toothpaste is used on a regular basis and to screen children for early signs of early childhood caries. A home visit will be undertaken if families find it difficult to attend, miss an appointment or the AHW thinks a home visit is the best way to maintain contact with the family.

This is an innovative approach which responds to the severely limited availability of dental personnel within Aboriginal communities, the very early onset of the disease in Aboriginal children, and recognizes the importance of AHWs to local communities. Early childhood caries develops at a time when contact with dental personnel is very limited in comparison to the regular contact young families have with Aboriginal Health Workers. In addition the active recruitment to the program by trusted local AHWs will overcome the problem that individuals from deprived backgrounds are less likely to consent to targeted preventive intervention schemes
[8,9].

The training program for AHSWs to explain how to implement the program has been tested and the supporting information leaflets have been piloted in collaboration with Aboriginal families. Both evaluations were positive in terms of their appropriateness and potential sustainability. The pilot data have been used to develop the protocol for a Phase II evaluation which will determine whether there is sufficient promise to warrant the investment in a large scale confirmatory Phase III cluster randomized trial. The development and evaluation of a program to improve oral health deliverable by community health personnel is relevant not only to Aboriginal communities, but also to other groups with limited access to dental services, including rural and remote communities throughout Australia.

## Methods/Design

The aim of the program of research is to address the need to improve the oral health of Aboriginal children
[10-12]. The objective of the study is to build upon the success of the pilot work, using a phase II single arm trial design to gather preliminary evidence on the effectiveness of the program offered to Aboriginal children from six months of age who are at risk of dental caries. The program will be assessed over a period of 2 years to investigate not only the effectiveness, but also its feasibility and to inform the design of a subsequent confirmatory randomised phase III trial. The research follows the MRC framework for the design and evaluation of complex interventions to improve health
[13]. The primary endpoint is the prevalence of early childhood caries at 30 months of age. Secondary endpoints include: changes in primary caregivers dental knowledge over time; number of episodes of dental care; impact of oral health problems on the family and qualitative measures of the program to assess its acceptability to the families. In addition the managers and Aboriginal Health Workers will be interviewed to record their views on the overall feasibility and sustainability of the program
[14].

The pilot work and consultation with ACCHSs led to the development of the dental health education program which is characterized by the following strategies:

Delivery by trained Aboriginal Health workers;

Support for health oral behaviours offered to families with young children;

Focus on control of the night time bottle, toothbrushing and use of fluoride toothpaste;

Free toothpaste, and toothbrushes for all the family together with a ‘sippy’ (trainer) cup for the child;

Restricting the frequency of the consumption of sugary snacks and drinks.

Careful attention to the cultural appropriateness of teaching materials.

The development of the ACCHSs capacity to provide oral health support to vulnerable families through the development of the role of AHWs is based on Goodman’s model of organizational change
[15].

The development of the oral health role of Aboriginal Health Workers is strongly supported by the National Aboriginal Community Controlled Health Organisation
[16], the Australian Dental Association
[17], Australia‘s National Oral Health Plan
[18], and the National Aboriginal and Torres Strait Islander Oral Health Workshop
[19]. Despite the extent of this support and the National Aboriginal Community Controlled Health Organization calling for the development of this role for over a decade there has been little sustainable development of the role of AHWs, and there has been no evaluation of the impact of such a role on the oral health of Aboriginal families. The disconnect between policy and practice in this area and the identification of facilitators and barriers to the development of this role has been the subject of recent research
[20].

The program focuses on family/carers because they significantly influence whether a child will develop Early Childhood Caries (ECC) and will be responsible for establishing long lasting family norms of behaviour regarding tooth brushing behaviour and diet
[21,22]. In order to support family/carers, AHWs will, systematically at predetermined intervals, provide them with oral health products, education materials, advice specific to the dental needs of the child and screen for early signs of ECC. This is an innovative approach to the prevention of oral disease in Aboriginal communities which contrasts the current model, whereby health education is delivered at irregular intervals.

The development of family knowledge and norms about the value and care of the primary dentition is important because many parents have the ‘commonsensical belief’ that if teeth do not hurt there are no dental problems
[23,24]. Given this belief and the rapid progression of the disease, dental care may not be sought until the child requires hospitalization for dental extractions under general anaesthesia. Hence, the inclusion of oral health screening is an integral part of the program.

The value of strategies which focus on families with young children is further emphasised by research which has shown that a child with one carious lesion is five times more likely to develop a further carious lesion than a child with no dental caries
[25]. This difference in risk is of major significance and demonstrates that early intervention to maintain a child’s oral health is the most logical and practical preventive strategy.

A lack of family carer access to dental health education and oral care products is a major barrier to maintaining a healthy mouth. Kruger et al
[26] reports a significant lack of oral health awareness among Aboriginal people. The National Rural Health Alliance reports that 30 percent of Indigenous children do not own a toothbrush
[27]. A study of Northern Territory Aboriginal communities reported that only 20 percent of children used toothpaste daily and most did not begin using toothpaste until the age of four
[28]. The AIHW reports that ‘Less than 5 percent of remote Aboriginal and Torres Strait Islander pre-school children brush their teeth on a regular basis
[6]. Causes identified for low use of toothbrushes and fluoride toothpastes include poor levels of carer education, high purchase costs and difficulties in establishing tooth brushing routines. The proposed program addresses these crucial barriers to the prevention of early childhood caries in Aboriginal families. AHWs will provide vulnerable families with advice on effective tooth brushing, use of fluoride toothpastes and support the development of these behaviours by the distribution of oral hygiene products and materials including toothbrushes, fluoride toothpaste and trainer cups
[29]. These preventive strategies are based on high quality evidence derived from large population based randomized controlled trials and systematic reviews
[30] and show a benefit when used over time. Therefore the theoretical construct underpinning the program is the tailoring of the oral health message to the specific oral health and psychosocial needs of Aboriginal families and their children
[31].

The dental health education program and the research instruments have been piloted with Aboriginal families, Aboriginal Health Workers and aligns with the Aboriginal Health and Medical Research Council policies on partnerships with Aboriginal Communities.

The primary endpoint for the study will be:

The prevalence of ECC at the age of 30 months. These data will be compared with similar children aged 30 months participating in the Aboriginal communities in the first year of the program implementation.

The secondary endpoints include:

Changes in the oral health knowledge of the primary care giver over time.

Early referral for dental care, if the oral health screening by the Aboriginal health workers notes a problem.

Impact of the child’s oral health on the family.

Acceptability of the program recorded by interviewing parents and AHWs at the end of the program.

Sustainability assessed by interviewing managers of the participating Aboriginal Community Care Health Services.

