### Study design

The study is designed to monitor a longitudinal oral health education program for Aboriginal children aged 6 months followed for 2 years. In order to assess the effect on dental caries, a sample size of 150 participants will provide at least 80 percent power at the two sided 95 percent level of significance to distinguish between a prevalence of 2 versus 1.6 ECC ( ECC includes decayed ,missing and filled primary teeth ) at 30 months allowing for as much as a 33% attrition rate (chosen following discussions with AHWs on population movement). The reference rate for ECC is informed by data provided by the Centre for Oral Health Strategy, New South Wales (personal communication and work by Jamieson et al
[6]). The forward projection is that the participating children will have a reduction in the mean ECC score of 20 percent, to 1.6. This is highly plausible and is based on previous trials. For example a recent study where fluoride toothpaste was posted to families living in low socio-economic areas of Northern England reported a 16 percent reduction in dental caries in young children
[32]. No personal advice was offered. An Australian study reported a 33 percent reduction in dental caries
[33,34], following a health education program which included the application of topical fluoride.

The rejection of the null hypothesis will be considered indicative of a clinically significant benefit, and would provide a strong case for proceeding to a Phase III evaluation.

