### Data collection

Information on baseline and subsequent visits (Figure
1) will be collected by the AHWs utilizing a structured questionnaire which has been piloted in an Aboriginal community.

The key topics for intervention are:

Bottle use, when and what to put in it.

Tooth brushing – using the tooth brush

Toothpaste - using the toothpaste, how much to put on the brush and safe storage

Dietary habits – reported changes in the consumption of sugary snacks and drinks

AHWs screen for caries
[35] – positive/negative

Reported dental problems

At the final 30-month assessment the carers will be asked about their perceptions of the feasibility, and acceptability of the program. In addition selected questions from the Dental Discomfort Scale
[36] and the Being a Mother Scale
[37] will be included in the assessment. The Aboriginal Health Workers and the senior management team at each AMS will be interviewed to record their views on the facilitators and barriers to the wider implementation of the program. All interviews will be recorded, transcribed and analyzed for recurrent themes.

The end of trial dental assessment will be undertaken by a calibrated examiner using the same diagnostic criteria when collecting the dental caries data on the historical reference group.

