### Statistical analysis

The primary analysis will be an evaluation of the estimated prevalence of caries at 30 months in relation to the null hypothesis that the rate is 2. Descriptive analyses of other endpoints will be applied using methods appropriate for continuous and categorical data. Estimates will be presented with two-sided 95 percent confidence intervals.

The qualitative data from the interviews will be analyzed , using the ‘framework’ method
[38]. The qualitative data will be fractured and examined for key topic areas. The data will then be systematically coded according to the topic areas and thematic charts (in spreadsheet form) will be constructed. Summaries of the relevant parts of transcripts will be written into the charts so that each case may be examined across a range of different and emerging themes
[38].

The proposed study is rare in health promotion research in that it is not a ‘before and after’ design but is longitudinal, building information and capacity over time
[39]. The longitudinal design helps the investigative team to test for mediation effects in a more rigorous manner than cross sectional designs
[40]. For example the multi-wave nature of the assessments delivers the following methodological advances:

i. prevention on the reliance of retrospective reports of health behavior from mothers (removal of memory biases);

ii. reliable baseline latent variables of fluoride use and oral health (reducing bias of measurement error);

iii. enable the testing of growth models and unbiased parameter estimation of the fluoride intervention using resampling methods (bootstrapping). This third improvement would be made possible by controlling for concurrent baseline disease levels. Cole and Maxwell
[39] suggest that Structural Equation Modelling (SEM) will greatly assist in testing the direct and indirect effects of a longitudinal intervention. Crucial is the development of a model which can reduce bias frequently inherent in two wave designs. These are sometimes referred to as ‘half-longitudinal’
[41]. The proposed design therefore has innovative features not utilized in previous caries prevention programs which will enable true longitudinal investigation benefiting from the latest developments in statistical modeling.

One potential model which could be assessed utilizing Structural Equation Modeling is shown in Figure

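### The primary endpoint promises a comparison with reference children, but the primary test and the power use a fixed outside value of 2, so rejection need not mean program benefit

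*Protocol article*

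**What the plan says.** Two comparators are given for the same endpoint.

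- **Reference children.** The Abstract says the clinical data at 30 months will be "compared with a reference population of similar children when the study began". Methods/Design repeats this directly under the primary endpoint: "These data will be compared with similar children aged 30 months participating in the Aboriginal communities in the first year of the program implementation". Data collection adds that the final examination is done "using the same diagnostic criteria when collecting the dental caries data on the historical reference group".
- **A fixed value.** Statistical analysis defines the primary analysis as an evaluation of 30-month caries "in relation to the null hypothesis that the rate is 2". It does not mention reference children. On the origin of the value, Study design says: "The reference rate for ECC is informed by data provided by the Centre for Oral Health Strategy, New South Wales", citing a personal communication and published work. The trial is sized "to distinguish between a prevalence of 2 versus 1.6 ECC" with 150 participants, at least 80% power, a "two sided 95 percent level of significance" and up to 33% attrition.

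Study design also says how the result will be read: rejecting the null will count as a clinically significant benefit and as a strong argument for a Phase III trial.

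**The concern.** The article names a concurrent or recent local comparator for its primary endpoint, then writes a primary test in which that comparator plays no part. This is more than detail left to an analysis plan. Both the comparator and the test are stated, they differ, and an analyst could follow either and reach a different conclusion.

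The difference matters because of how rejection is read. A test against 2 asks whether the program children's mean differs from 2. It answers whether the program worked only if 2 is about what these children would have had without it. If untreated children in these six services average a little under 2, an ineffective program can look beneficial and trigger a Phase III trial. If they average above 2, an effective program can look useless. In addition, the sample size carries no allowance for sampling error in a reference group, so the stated power does not apply to the comparison promised under the primary endpoint.

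**Working it through.** **Inputs from the protocol article.** Null 2, alternative 1.6 (difference 0.4), two-sided 5% level, at least 80% power, N = 150, 33% attrition (Study design and Statistical analysis). Evaluable children: 150 × 0.67 = 100.5, taken as 100.

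**Assumptions.** No SD is stated, so I use Poisson variance (variance equal to the mean), with SD = 2 as a more dispersed alternative. No reference-group size is stated, so m is a range.

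**1. Reproducing N = 150.** One-sample test against a constant, SD = √2 = 1.414:

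n = ((1.960 + 0.842) × 1.414 / 0.4)² = 98.1, so 99 evaluable; 99 / 0.67 = 148 enrolled.

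With variance 2 under the null and 1.6 under the alternative, 100 evaluable children give power 83.4%. Both agree with 150 and at least 80%. The stated sample size therefore behaves as a one-sample calculation with no error in the reference value.

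**2. If the untreated local mean μ is not 2 and the program has no effect.** The test declares benefit when the observed mean falls below 2 − 1.96 × √(2/100) = 1.723. The probability is Φ((1.723 − μ) / √(μ/100)).

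| μ | Poisson | SD = 2 (cut-off 2 − 1.96 × 0.2 = 1.608) |
|---|---|---|
| 2.0 | 2.5% | 2.5% |
| 1.9 | Φ(−1.29) = 9.9% | Φ(−1.46) = 7.2% |
| 1.8 | Φ(−0.58) = 28% | Φ(−0.96) = 17% |

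**3. The error in the other direction.** Suppose μ = 2.2 and the program achieves its full 20% reduction, giving 2.2 × 0.8 = 1.76. The chance of a significant benefit is Φ((1.723 − 1.76) / √(1.76/100)) = Φ(−0.28) = 39%, against 83% if the untreated mean were 2.

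**4. Power for the comparison stated under the primary endpoint.** Program children: 100 evaluable, mean 1.6. Reference children: m, mean 2. Power = Φ(0.4 / √(1.6/100 + 2/m) − 1.96).

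| m | SE | Power |
|---|---|---|
| 100 | 0.190 | 56% |
| 150 | 0.171 | 65% |
| 300 | 0.151 | 76% |

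For 80%: m = 2 / ((0.4/2.802)² − 0.016) ≈ 456. These figures take the variances at the alternative, which is slightly generous: as m grows without limit the formula gives 88.5%, above the 83.4% in step 1. Overdispersion lowers them. With SD = 2 in both groups and m = 100, power is 29%.

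**The case against.** A fixed null is an accepted choice for a single-arm Phase II study that seeks preliminary evidence before a randomised trial. The Statistical analysis section does not rule out a further comparison with the reference children. The reference group may also be a poor comparator: its size and sampling are not described, and Recruitment notes that the health workers know which families most need support, so program families may differ from reference families. These points stand. They mean that the two-group analysis is not the only acceptable repair. They do not remove the mismatch between the named comparator and the written test, or the reading of rejection as benefit.

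Several stronger readings are tempting, and the article does not support them:

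- A reader might infer that the test is invalid unless the local mean is exactly 2. A test of a mean of 2 is valid whatever the local mean, and small departures do limited harm. What fails is its interpretation as a program effect.
- A reader might point to an untreated mean of 1.6, where benefit would be declared 83% of the time. That supposes a constant wrong by the whole planned effect, and nothing in the article suggests it.
- A reader might infer an inflated type I error from inserting the observed reference mean as if it were known. The article does not propose that.
- A reader might infer that one examiner sees both groups, or that reference data are already in hand for every service. The article states common diagnostic criteria only. It gives no breakdown by service and no collection status.

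**Conclusion.** The point holds. The comparator named in the Abstract and under the primary endpoint conflicts with the test in Statistical analysis, and Study design reads more into rejection than that test can show. As written, the trial could support a wrong conclusion in either direction.

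For a constant that is 0.1 or 0.2 too high, the false-benefit rate is about 10% or 28% under Poisson variance, and 7% or 17% with SD 2, against a nominal 2.5%. How far 2 lies from the local untreated mean cannot be known from the article, so these figures show sensitivity and do not predict what will happen. The claim of 80% power is credible for a one-sample test under Poisson variance. It does not hold for the promised comparison unless the reference group has about 456 children or more. That figure and the 56% to 76% range rest on the assumed variance and the assumed reference-group sizes.

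**What to change.** Reconcile the Abstract, Methods/Design, Study design, Data collection and Statistical analysis sections.

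**Preferred.** Make the primary analysis a two-group comparison of the mean number of decayed, missing and filled primary teeth at 30 months between program and reference children. Use a count model that allows for overdispersion, report a rate ratio with its 95% confidence interval, and adjust for medical service and age at examination where the reference data record them. Keep 2 as a planning value. State the size of the reference group and restate the power for this comparison, without enlarging the trial. Restoring 80% with equal groups would take 177 evaluable children per group, or 177 / 0.67 ≈ 265 enrolled in the program, above the potential 216 in Recruitment. A lower, honest figure is the proportionate answer for a Phase II study.

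**Alternative.** If 2 stays as the primary benchmark, state its source and precision, name the reference-group comparison as a key supportive analysis, and amend Study design so that rejection alone is not taken as program benefit.

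**Cost.** The alternative costs only wording. The preferred route costs wording and a less favourable stated power, and it depends on child-level reference data being available, which the authors should confirm.
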